## Abstract

**Background:**

Post-market long-term surveillance data for aortic endovascular devices are essential due to evolving regulatory standards and clinical practice demands. Building upon the successful Global Registry for Endovascular Aortic Treatment (GREAT), comprehensive real-world data is required to address current gaps in long-term device performance and patient outcomes. Thus, the purpose of this manuscript is to describe the protocol, objectives, and anticipated outcomes of the Gore Together Aortic Registry, designed for extensive real-world evaluation of the performance and clinical outcomes of aortic endovascular devices.

**Methods:**

The Gore Together Aortic Registry is an international, prospective, observational registry initiated in response to increased regulatory emphasis on long-term post-market surveillance. This registry will enroll approximately 3,355 adult patients (≥18 years old) from over 170 global clinical centers, undergoing routine clinical care with GORE® aortic endovascular devices. Enrollment commenced based on standard clinical application, with data and imaging collection beginning at the time of hospitalization, and at each follow-up period.

**Ethics and dissemination:**

Primary registry outcomes include technical deployment success, measures of device or procedural adverse events, including endoleaks, as well as post-procedure reinterventions. Individual modules can tailor their reporting to address pertinent needs that may include dissection characterization, neurological complications or renal dysfunction. Follow-up is collected per standard of care with the potential to capture up to 10 years of data based upon device need. Patient enrollment is ongoing; no results are reported at this stage.

**Conclusion:**

The Gore Together Aortic Registry aims to deliver robust and granular real-world data regarding mid-term clinical outcomes of aortic endovascular devices, enhancing patient care strategies and meeting evolving global regulatory expectations. Results will guide clinical decisions, inform regulatory oversight, and potentially improve device safety and efficacy.

**Clinical trial registration:**

The individual modules of the Gore Together Aortic Registry are registered in ClinicalTrials.gov as:
https://clinicaltrials.gov/study/NCT06218875, identifier NCT06218875https://clinicaltrials.gov/study/NCT06507865, identifier NCT06507865https://clinicaltrials.gov/study/NCT06658730, identifier NCT06658730

## Introduction

1

In 2010, a large observational registry named the Global Registry for Endovascular Aortic Treatment (GREAT; ClinicalTrials.gov Identifier: NCT01658787) was initiated to capture real-world clinical outcomes and severe adverse events associated with commercially available endovascular aortic devices. This registry enrolled data from over 5,000 patients across multiple international regions, including Europe, North America, South America, and Australia (1). The registry has provided substantial evidence, that have contributed to our understanding of endovascular treatment outcomes, such as device durability, secondary interventions, and patient survival (Supplement 1).

Since the establishment of the GREAT registry, global regulatory frameworks for medical devices have evolved, demanding rigorous post-market surveillance and comprehensive, real-world data collection to ensure long-term device safety and effectiveness (2–4). Notably, regulations such as the European Union's Medical Device Regulation (EU MDR 2017/745) and initiatives by the U.S. Food and Drug Administration (FDA), such as the National Evaluation System for Health Technology (NEST), emphasize continuous, detailed monitoring of clinical outcomes and patient safety in real-world settings (5). These regulatory shifts highlight the increasing demand for high-quality, real-world data to support clinical decision-making, post-market surveillance, and regulatory compliance.

In response to these regulatory demands and the need for improved patient-centered evaluations, a new international observational registry, the Gore Together Aortic Registry (Together Registry), was established. This registry is structured to systematically collect standardized clinical outcomes and patient-reported outcomes (PROs), including quality-of-life measures and symptom relief (6–8). By integrating standardized data collection methodologies and expanding geographical scope, the registry aims to enhance the understanding of clinical outcomes and long-term device performance, facilitating comparisons across patient populations and device types. In addition, imaging data will be included, allowing detailed interventional analysis, related outcomes, as well as providing future opportunities for robust morphological assessment of aneurysm behavior following endograft implantation.

Ethical considerations and adherence to stringent data privacy standards, such as the General Data Protection Regulation (GDPR) and the Health Insurance Portability and Accountability Act (HIPAA), are integral components of the Together Registry design. These rigorous standards ensure patient confidentiality and data integrity.

This manuscript provides a detailed overview of the Together Registry, describing its objectives, methodology, and anticipated contributions to clinical practice and regulatory frameworks through robust and comprehensive real-world data.

## Methods and analysis

2

### Study design

2.1

The Together Registry employs a prospective, observational, multicenter design, aiming to evaluate real-world outcomes of endovascular aortic interventions and foster collaboration across academic and community centers across the world. This registry systematically captures data across multiple device types utilized in the treatment of abdominal and thoracic aortic pathologies. It assesses the performance of multiple devices within Gore's Aortic portfolio across three distinct modules, including the GORE® EXCLUDER® Conformable AAA Endoprosthesis (EXCC), and GORE® EXCLUDER® Iliac Branch Endoprosthesis (IBE) [NCT06218875], GORE® TAG® Conformable Thoracic Stent Graft with ACTIVE CONTROL System (CTAG-AC) [NCT06658730] and GORE® TAG® Thoracic Branch Endoprosthesis (TBE) [NCT06507865]. Unlike randomized controlled trials, this registry does not prescribe specific procedural methodologies or interventions beyond routine clinical care, thus ensuring the collection of representative real-world clinical applications and outcomes from diverse practice settings.

### Ethical considerations and regulatory compliance

2.2

The registry adheres to international research and regulatory guidelines, including Good Clinical Practice (GCP) as defined by ISO 14155:2020 and ICH E6 (R2), as well as regulatory requirements established by the FDA, the European Medicines Agency (EMA), the Ministry of Health, Labour and Welfare (MHLW) and other applicable health authorities. Institutional Review Board (IRB) or Ethics Committee (EC) approval is obtained for all participating sites, ensuring compliance with ethical principles and patient protection standards. Data governance is maintained through rigorous de-identification protocols and adherence to the General Data Protection Regulation (GDPR) and the Health Insurance Portability and Accountability Act (HIPAA), safeguarding patient confidentiality.

Protocol deviations will be systematically reviewed to confirm classification and ensure appropriate documentation. Any identified trends or concerns will undergo further evaluation and, when necessary, corrective measures or protocol modifications will be implemented to minimize recurrence, thereby maintaining consistency with regulatory and ethical standards. Adverse events and device deficiencies will be subject to systematic review by an Observational Safety Monitoring Board, which includes 3 to 5 experts in the field with extensive clinical experience. Reported events, including those from comparator groups, will be evaluated to identify potential safety signals, confirm coding accuracy, and determine whether further investigation or communication with stakeholders is required. Signals suggesting a potential health threat will prompt timely escalation to ensure patient safety and regulatory compliance. The registry protocol was approved by the Institutional Review Board or Independent Ethics Committee at each participating institution, and all participating sites complied with their respective local regulatory and ethical requirements.

### Participants and enrollment

2.3

As a real-world registry and collaboration across academic and community centers, enrollment is structured to ensure comprehensive regional representation of diverse patient populations through a multi-site approach, encompassing 96 clinical centers for the EXCC/IBE module, 57centers for the CTAG-AC module, and 26 centers for the TBE module (Table 1). The total number of enrolled patients will vary by module. The EXCC/IBE module targets up to 2,000 patients (1,700 and 300, respectively), the CTAG-AC module aims to enroll 1,200 participants, and the TBE module includes approximately 155 subjects. Follow-up duration is tailored to the characteristics of the devices under investigation. The EXCC/IBE, and CTAG-AC modules follow patients for ten years post-procedure, whereas the TBE module has a follow-up period of two years. The duration of the latter was considered sufficient for assessing mid-term device performance, particularly in the context of evaluating regional variations in device utilization and procedural outcomes. This approach is supported by the existence of separate, ongoing longitudinal data collection efforts designed to capture long-term outcomes (9).

**Table 1 T1:** Together aortic registry enrollment.

Devices	Clinical Sites	Enrollment Target			Total
	Total No. of Sites^a^	North America	EMEA^b^	Asia Pacific^c^	
GORE® EXCLUDER® EXCC module	96	790	505	405	1,700
GORE® EXCLUDER® IBE Module		110	45	145	300
GORE® TAG® Conformable with Active Control Thoracic Stent Graft Module	55	600	300	300	1,200
GORE® TAG® Thoracic Branch Endoprosthesis (TBE) Module	26	–	120	35	155

a This is an approximate number as the site selection process is ongoing.

b Europe, Middle East and Asia region.

c Australia, Japan, New Zealand.

### Patient and public involvement

2.4

This research was conducted without patient or public involvement. Patients and members of the public were not involved in the design of the study, the selection of outcome measures, the conduct of the research, or the interpretation and dissemination of the results. The Together Registry is a prospective observational clinical registry designed to collect data arising from routine clinical care, and methodological decisions were driven by clinical and regulatory requirements. Participants provide informed consent for data collection in accordance with local ethics approvals.

### Patient population and eligibility criteria

2.5

Patients eligible for inclusion in the registry are those requiring aortic intervention with a Gore aortic endovascular device as part of their standard clinical care. To ensure broad applicability and facilitate the collection of real-world data, inclusion criteria encompass individuals aged 18 years or older who have undergone or are planned to undergo treatment with an eligible device (Table 2). Subjects will be included irrespective of whether the device was used within or outside its labeled indications for use, thereby capturing the full spectrum of real-world practice patterns.

**Table 2 T2:** Together registry inclusion and exclusion criteria.

Inclusion Criteria	Exclusion Criteria
1. Patient or legally authorized representative (LAR) provides written authorization and/or consent per institutional and geographical requirements. 2. Patient has been or is intended to be treated with an eligible registry device.^a^ 3. Patients ≥18 years of age at the time of informed consent signature.	1. Patient who is, at the time of consent, unlikely to be available for standard-of-care (SOC) follow-up visits, as defined by the site's guidelines and procedures. 2. Patients have exclusion criteria required by local law. 3. Patients are currently enrolled in or plans to enroll in any concurrent investigational drug and/or investigational device study within 12 months of Together Registry enrollment^b^. Subjects cannot be enrolled in another Together Registry module protocol.

a The intent to treat a patient with a Gore product must be made prior to soliciting for registry participation. If pre-procedure consent is not feasible due to emergent situation, consent from the subject or LAR prior to the time of discharge for the index procedure is acceptable.

b The term “study” does not apply to other observational registries or quality improvement projects. Collection of EXCC or IBE performance from interventional studies may be permissible provided device application is not investigational and there are no novel requirements that alter follow-up conduct (i.e., protocol-mandated interventions).

Written informed consent, following guidelines from the Declaration of Helsinki and Good Clinical Practice (GCP), is mandatory for participation, as it constitutes a fundamental ethical and regulatory requirement in clinical research. Prior to enrollment, all patients or their legally authorized representatives will receive comprehensive information regarding the study's objectives, procedures, potential risks and benefits, and their rights as research participants from a health care professional or trial designee at the respective clinical site. Participants retain the right to withdraw from the study at any stage time without impacting their medical care. Key exclusion criteria include anticipated inability to complete follow-up, concurrent enrollment in other investigational studies, and any legal or regulatory prohibitions affecting participation (Table 2). To widen the generalizability of the participants, acute patients could also be enrolled after implantation of an unplanned aortic devices in an emergency setting after providing written consented.

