### Follow-up and clinical outcomes assessment

2.7

The registry evaluates a range of clinical and device-related outcomes, categorized as primary and secondary measures (Table 4). The primary outcomes of interest include technical deployment success, all-cause and lesion-related mortality, and device-related adverse events such as endoleaks, device migration, loss of branch patency, renal function deterioration, and neurological complications, including stroke, paraplegia, and paraparesis (Table 4). Secondary outcomes are device specific and encompass access-related complications, new-onset renal failure, false lumen remodeling in TEVAR-related registries, and health economic parameters, including hospital length of stay and ICU admission rates, depending on the module. Additionally, the EXCC/IBE module assesses quality of life measures, using the EQ-5D-5L, a validated instrument available in over 150 language versions through the EuroQol Research Foundation, ensuring applicability across the registry's geographically diverse participating centers (10, 11), incidence of erectile dysfunction, and buttock claudication as part of long-term follow-up.

**Table 4 T4:** Primary and secondary outcomes for each module.

Primary Outcomes		
• Deployment Technical Success (index procedure only)^a^ Assessment of the following through all follow-up windows (unless indicated) ○ Mortality (all-cause, lesion-related) ○ Device and Treatment-related Adverse Events (AEs), including: ▪ Lesion rupture (treated area) ▪ Lesion enlargement (treated area) ▪ Endoleaks ▪ Device migration ▪ Loss of aortic/branch patency ▪ New onset renal failure (w/in 30 days of the procedure) ▪ Renal function deterioration ○ Serious Adverse Events (SAEs) ○ AEs with unknown causal relationships ○ Device integrity events (e.g., fracture, kinking, compression) ○ Reintervention		

Secondary Outcomes		
AA Module	TA Module	TB Module

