### Statistical analysis

2.9

As a real-world registry, no statistical hypotheses are specified. By default, statistical testing will test for two-sided differences across arbitrary subgroups to better understand clinical outcomes. All data will be included in their appropriate analysis as intention to treat.

Statistical analyses will employ a combination of descriptive and inferential methodologies to ensure comprehensive evaluation of patient outcomes. Kaplan–Meier survival analyses estimate freedom from mortality, reintervention, and major adverse events over time. Cox proportional hazards models will be used to identify predictors of device failure and clinical complications, while multivariate regression models assess the influence of patient demographics, procedural variables, and anatomical characteristics on long-term outcomes. To provide contextual comparisons, the registry integrates historical data from prior observational studies, allowing for benchmarking of device performance against established clinical standards.

The contrast-enhanced computed tomography (CT) component of this study provides a robust foundation for quantitative imaging analysis and potential future applications of machine learning. Contrast CT offers high spatial and temporal resolution that enables precise assessment of vascular anatomy, device positioning, and procedural outcomes. Beyond its immediate diagnostic and procedural value, the imaging dataset has been structured to support the extraction of radiomic and morphological features that could inform predictive modeling. This framework allows for future implementation of advanced analytical approaches, including machine learning-based image analysis, to identify subtle imaging biomarkers and optimize outcome prediction in endovascular interventions.

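### Emergency patients may consent after implantation and have follow-up availability judged at that point, so early deaths can drop out of primary outcomes labelled intention to treat

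*Protocol article*

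**What the plan says.** Section 2.5 of the protocol article makes consent a condition of entry: written consent "is mandatory for participation, as it constitutes a fundamental ethical and regulatory requirement in clinical research". Consent is normally sought before the procedure, but Table 2, footnote a, makes an exception: "If pre-procedure consent is not feasible due to emergent situation, consent from the subject or LAR prior to the time of discharge" is acceptable. The text below Table 2 repeats that "acute patients could also be enrolled after implantation of an unplanned aortic devices in an emergency setting", once written consent is given. Inclusion criterion 2 fits this route: "Patient has been or is intended to be treated with an eligible registry device".

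Exclusion criterion 1 removes a "Patient who is, at the time of consent, unlikely to be available for standard-of-care (SOC) follow-up visits", with availability defined by each site's own guidelines and procedures.

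In Section 2.7, Table 4 lists technical success at the index procedure and all-cause and lesion-related mortality among the primary outcomes. Section 2.10 makes the index procedure and 30 days separate publication milestones. Section 2.9 states: "All data will be included in their appropriate analysis as intention to treat".

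**The concern.** For a patient consented before the procedure, entry cannot depend on what happens in the operating room or soon after. In the emergency route it can. The patient must have consent given, personally or by a representative, and must then look available for follow-up. Both conditions are met or failed after implantation. A patient who dies early may fail the first, and a patient who is dying when consent is sought fits the wording of the second.

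Entry to the cohort can thus depend on a primary outcome that has already happened. An intention-to-treat label does not bring back patients who never entered. At stake are the index-procedure and 30-day results, which are the first to be published and would be read as real-world early mortality. The registry says it captures the full range of practice, and it admits emergency patients specifically to widen generalizability.

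**Working it through.** **Passages side by side**

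| Step | Patient consented before the procedure | Emergency patient consented afterwards |
|---|---|---|
| Consent (2.5, footnote a) | before implant | after implant, up to discharge |
| Exclusion 1 judged (Table 2) | before any outcome | deployment result and early course known |
| Death soon after implant | patient already enrolled, death counted | counted only if consent came first and the patient was not judged unavailable |
| Described as (2.9) | intention to treat | intention to treat |

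Footnote a also requires the decision to use the device to precede any approach about the registry. Once the device is implanted that is already met, so it does not prevent the selection.

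**Illustration of size**

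The article states no figure on this point. The following are assumptions:
- f = share of emergency cases, all taking the late-consent route: 20%
- m = early mortality in emergency cases: 20%
- e = early mortality in elective cases: 2%
- s = share of emergency early deaths never enrolled: 0% to 100%
- all surviving emergency patients and all elective patients are enrolled

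True early mortality = (1 − f)e + fm = 0.80 × 0.02 + 0.20 × 0.20 = 0.016 + 0.040 = 5.6%.

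Observed = [(1 − f)e + fm(1 − s)] / (1 − fms).

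| s | Calculation | Observed | Shortfall |
|---|---|---|---|
| 0% | 0.056 / 1 | 5.6% | none |
| 25% | (0.016 + 0.030) / 0.99 = 0.04646 | 4.6% | 1.0 point |
| 50% | (0.016 + 0.020) / 0.98 = 0.03673 | 3.7% | 1.9 points |
| 100% | 0.016 / 0.96 = 0.01667 | 1.7% | 3.9 points |

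Within the emergency group alone, observed = m(1 − s)/(1 − ms). At m = 20% this is 0.15/0.95 = 15.8% for s = 25% and 0.10/0.90 = 11.1% for s = 50%.

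**Range.** With e fixed at 2%, f from 10% to 40%, m from 10% to 30% and s from 25% to 90%, the relative understatement runs from 9% (true 2.8%, read as 0.0255/0.9975 = 2.6%) to 80% (true 13.2%, read as 0.024/0.892 = 2.7%).

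**Yardstick.** Section 2.8 gives an exact 95% interval width of 3.5% for a 10% rate at N = 1,200 in the thoracic (CTAG-AC) module. A Clopper-Pearson interval gives 8.36% to 11.84%, a width of 3.48%, which agrees. By the same method the half-width at a 5.6% rate is about 1.3 points at N = 1,200 and about 4.0 points at N = 155. Under these assumptions, a shortfall at s = 50% would exceed the sampling error in the larger module but not in the TBE module.

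**The case against.** The strongest reply is that late consent is a disclosed trade-off. Without it, many emergency patients could not enter at all, and the registry would be less representative. The registry tests no prespecified hypothesis and has no randomised arms, so intention to treat is loose wording rather than an invalid comparison. Section 3.1 also acknowledges selection bias. This stands as a reason to keep the route. It does not answer the point: Section 3.1 speaks of variability in clinical decision-making and patient selection across centers, and discusses loss only after enrollment.

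Several stronger readings are tempting, and the documents do not support them:

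- **Severe complications are excluded by rule.** A reader might infer that a patient with a stroke or paraplegia is screened out. A representative can consent for an incapacitated patient, and exclusion 1 leaves availability to site procedures. Such a patient may be excluded but need not be.
- **The bias always favours the device.** This is not shown. The consent window closes at discharge, so a patient with a non-fatal complication may stay longer and have more time to consent, while an uncomplicated patient leaves unconsented. For reintervention and non-fatal events, selection could run the other way.
- **Late enrollees are credited with guaranteed survival time.** Section 2.3 counts follow-up years from the procedure, but Section 2.9 names Kaplan–Meier and Cox methods without stating a time origin or entry rule. An article may leave that to the full plan. It is a risk to guard against, not a stated error.
- **The whole registry is affected.** Patients consented before the procedure are not.

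**Conclusion.** The point holds for the emergency route. Followed as written, the consent rule and exclusion 1 can leave out patients who die before consent or are moribund when it is sought. Neither footnote a nor Section 3.1 repairs this. Early mortality is expected to be understated. The effect on non-fatal complications is uncertain, and technical success is affected only as far as failed deployments go with the missing deaths.

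The size cannot be known from the article. The illustrative fall from 5.6% to between 4.6% and 1.7% rests on assumed emergency share and mortality, and on enrolling every surviving emergency patient; it disappears if no early deaths are missed. The full protocol may already hold a screening log or a rule for deceased patients. The point does not rely on their absence but on what the article fixes: when consent may be given, when availability is judged, and what the resulting analysis is called.

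**What to change.** 1. Reword exclusion 1 so that availability is judged on the patient's status and circumstances before the index procedure, not on the course after it. This does not recover patients who die before anyone consents; item 4 makes that loss visible.
2. Record the date and time of consent relative to implant. Report technical success and 30-day outcomes separately for patients consented before and after the procedure, alongside the overall figure. The pre-procedure group should not become the sole headline: if all emergency patients consent late, it would read about 2.0% under the assumptions above, further from 5.6% than most of the readings it would replace.
3. For mortality, add a sensitivity Kaplan–Meier and Cox analysis in which late-consented patients enter the risk set at consent. State that this corrects neither technical success nor consent that itself depends on outcome.
4. Where local rules allow, report counts of eligible treated emergency patients not enrolled, with reasons, including death before consent.
5. Do not describe the late-consented group as intention to treat.

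The cost is one eligibility wording change, one date/time field, non-enrollment counts from sites, some analysis code, and less precise estimates within each consent stratum. Enrollment is ongoing, so consent timing and non-enrollment are easier to capture now than to reconstruct later.
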